**Table 10. Criteria for decision of withdrawal of S-1 monotherapy**

| Item                       |                                | Criteria for withdrawal                                                                                                                                          | Criteria for resumption                                                                                          |
|----------------------------|--------------------------------|------------------------------------------------------------------------------------------------------------------------------------------------------------------|------------------------------------------------------------------------------------------------------------------|
| Blood toxicity             | White blood cell count         | $< 2,000/\text{mm}^3$                                                                                                                                            | $\geq 2,000/\text{mm}^3$                                                                                         |
|                            | Neutrophil count               | $< 1,000/\text{mm}^3$                                                                                                                                            | $\geq 1,000/\text{mm}^3$                                                                                         |
|                            | Platelet count                 | $< 75,000/\text{mm}^3$                                                                                                                                           | $\geq 75,000/\text{mm}^3$                                                                                        |
| Non-hematological toxicity | Total bilirubin                | $> 1.5$ mg/dL                                                                                                                                                    | $\leq 1.5$ mg/dL                                                                                                 |
|                            | AST and ALT                    | Greater than 100 IU/L                                                                                                                                            | 100 IU/L or less                                                                                                 |
|                            | Creatinine                     | $\geq 1.2$ mg/dL                                                                                                                                                 | $< 1.2$ mg/dL                                                                                                    |
|                            | Infection                      | Fever of suspected infection                                                                                                                                     | No fever of suspected infection                                                                                  |
|                            | PS                             | 2 or more                                                                                                                                                        | 0 to 1                                                                                                           |
|                            | Diarrhea, mouth ulcers         | Grade 2 or above                                                                                                                                                 | Grade 1 or below                                                                                                 |
|                            | Other non-hematologic toxicity | Grade 3 or above                                                                                                                                                 | Grade 2 or below
(However, the physician in charge may decide in his/her discretion to allow administration.) |
|                            | Others                         | Drug withdrawal is allowed when deemed necessary by the physician in charge due to the occurrence of adverse events that do not fall under the above categories. | Adverse event that caused withdrawal from the drug is in remission                                               |

Grade 4 non-hematologic toxicities (Grade 1 or higher for pulmonary inflammation) will result in discontinuation of protocol treatment.

#### 6.3.4. Criteria for dose reduction (Arm B)

When resuming dosing in patients with adverse events that meet the criteria for dose reduction specified in Table 11, the dose should be reduced one step at a time according to Table 12, “Dose reduction levels”. However, the minimum dose of S-1 is 50 mg/day, and the dose will not be increased again after a dose reduction. For adverse events other than those listed in Table 11, the S-1 dose may be reduced at the discretion of the physician in charge, again in accordance with the dose reduction levels listed in Table 12.

**Table 11. Criteria for dose reduction**

| Item                                     | Criteria for dose reduction                                                               |
|------------------------------------------|-------------------------------------------------------------------------------------------|
| White blood cell count                   | < 1,000 /mm  (Grade 4)                                                        |
| Neutrophil count                         | < 500 /mm  (Grade 4)
Febrile neutropenia (Grade 3 or higher)               |
| Platelet count                           | < 25,000 /mm  (Grade 4)
Grade 3 thrombocytopenia with platelet transfusion |
| Creatinine                               | ≥ 1.2 mg/dL                                                                               |
| Total bilirubin                          | ≥ 2.0 mg/dL                                                                               |
| Non-hematologic toxicity (except low Na) | Grade 3 or above                                                                          |

Grade 4 non-hematologic toxicities (Grade 1 or higher for pulmonary inflammation) will result in discontinuation of protocol treatment.

**Table 12. Dose reduction levels (dose reduction methods for S-1)**

| Body surface area                             | At the start of treatment
(FT equivalent) | descent level |                        |                        |                        |
|-----------------------------------------------|----------------------------------------------|---------------|------------------------|------------------------|------------------------|
|                                               |                                              | -1            | -2                     | -3                     | -4                     |
| < 1.25 m                          | 80 mg/day                                    | 50 mg/day     | Cessation of treatment | -                      | -                      |
| ≥ 1.25 m  and <1.5 m  | 100 mg/day                                   | 80 mg/day     | 50 mg/day              | Cessation of treatment | -                      |
| ≥ 1.5 m                           | 120 mg/day                                   | 100 mg/day    | 80mg/day               | 50 mg/day              | Cessation of treatment |

#### 6.3.3. Dose escalation (Arm B)

After the second course, if there are no adverse events that would result in withdrawal/reduction of the dose and the physician in charge determines that there are no safety issues, the dose of S-1 may be increased by one step only from the initial standard dose according to Table 13. Dose escalation levels.

The dose should not be increased in patients whose dose has been reduced since the first dose due to the CCR value at the time of registration ( $40 \leq \text{CCR} < 60$ ).

The dose should not be increased again in cases where the dose has been reduced.

Dose reductions for increased doses follow the dose reduction levels in Table 14.

**Table 13. Dose escalation levels**

| The method for the dose escalation of S-1     |                                          |                       |
|-----------------------------------------------|------------------------------------------|-----------------------|
| Body surface area                             | Initial standard dose
(FT equivalent) | Dose escalation level |
|                                               |                                          | +1                    |
| < 1.25 m                          | 80 mg/day                                | 100 mg/day            |
| ≥ 1.25 m  and <1.5 m  | 100 mg/day                               | 120 mg/day            |
| ≥ 1.5 m                           | 120 mg/day                               | 150 mg/day            |

**Table 14. Dose reduction levels for the cases with dose escalation**

| The method for the dose reduction for the cases with dose escalation of S-1 |                                        |                      |            |                        |
|-----------------------------------------------------------------------------|----------------------------------------|----------------------|------------|------------------------|
| Body surface area                                                           | Dose after increase
(FT equivalent) | Dose reduction level |            |                        |
|                                                                             |                                        | -1                   | -2         | -3                     |
| < 1.25 m                                                        | 100 mg/day                             | 80 mg/day            | 50 mg/day  | Cessation of treatment |
| ≥ 1.25 m  and <1.5 m                                | 120 mg/day                             | 100 mg/day           | 80 mg/day  | 50 mg/day              |
| ≥ 1.5 m                                                         | 150 mg/day                             | 120 mg/day           | 100 mg/day | 80 mg/day              |

## **7. Protocol treatment discontinuation, termination criteria, and subsequent therapy**

### **7.1. Criteria for discontinuation of protocol treatment**

If any of the following criteria are met, the physician in charge will discontinue protocol treatment

- 1) If protocol treatment cannot be started 28 days after the last day of S-1 treatment (which corresponds to 21 days after the scheduled start of the next course in Arm B) (in this case, the day after the last day of S-1 treatment is considered Day 1). Starting administration on the same day of the week is acceptable).
- 2) If a withdrawal of more than 28 days is required (in this case, the day after the last day of S-1 administration shall be considered as Day 1. Resumption on the same day of the week 4 weeks after the date of the last dose is acceptable)
- 3) When an adverse event that meets each of the dose reduction criteria occurs even if the S-1 dose is reduced to the lowest level  
Or if a Grade 4 non-hematologic toxicity (Grade 1 or higher for pulmonary inflammation) develops.
- 4) When an adverse event occurs that makes it difficult to continue administration
- 5) If the physician in charge determines that the disease has recurred
- 6) If the patient requests discontinuation
- 7) When matters that should be excluded from the subjects turned out after registration
- 8) Other cases in which the physician in charge deems it necessary to discontinue the study.

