#### Arm B: Daily administration of S-1 for 2 weeks followed by 1-week rest

S-1 is taken orally every day for 14 days (after dinner on Day 1 to after breakfast on Day 15), followed by a 7-day rest period, repeated every 3 weeks as a course. This is repeated every 3 weeks for a total of 12 months from the start date of the protocol treatment. No new course will be started after the same calendar day 12 months after the start date of the protocol. The final course of treatment should be administered until the equivalent of day 14. If administration cannot be started more than 28 days after the last day of administration, this study treatment will be discontinued (day 1 will be the next day after the last administration). The same day of the week 4 weeks after the last administration is acceptable).

Administration is repeated until one of the criteria for discontinuation of study treatment is met.

[figure not shown]

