### 6.3. Arm B: S-1 2-week administration followed by 1-week rest method

#### 6.3.1. Treatment schedule for Arm B (S-1 2-week administration followed by 1-week rest method)

**Administration cycle:** Oral administration every day for 14 consecutive days from Day 1 (after dinner on Day 1 to after breakfast on Day 15)

The drug is then withdrawn for 7 days, and this is repeated every 3 weeks for one course.

**End date of treatment:** Administration should be performed until the total treatment period from the protocol treatment start date has reached 12 months. No new courses should be started after the same calendar day 12 months after the protocol treatment start date. The final course of treatment should be administered until a date equivalent to day 14.

[figure not shown]

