#### 6.3.2. Course start criteria for Arm B (S-1 2-week administration followed by 1-week rest)

The start of the next course is decided after confirming that all of the criteria in Table 9 below are met on the day before or the day of the scheduled start of the course. If even one of the criteria is not met, administration is postponed, and administration is started as soon as the patient recovers.

However, for the start of the second and subsequent courses, **if these criteria are not met 21 days beyond the scheduled start of the next course, the study of the case will be terminated** (see figure below).

In the case of a postponement of the start of a course, the start date after the postponement shall be Day 1 of the course.

If recurrence is observed during the course of treatment, protocol treatment should be discontinued at that time.

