### 6.3.3. Criteria for in-course withdrawal and resumption (Arm B)

If an adverse event that meets the criteria in Table 10 develops during S-1 administration, S-1 will be withdrawn. If the adverse event has not resolved by the end of breakfast on Day 15, no further S-1 should be administered for that course. If the patient has not recovered from a Grade 4 non-hematologic toxicity (Grade 1 or higher for pulmonary inflammation), protocol treatment should be discontinued.

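### Protocol 7.1(1) equates two Arm B stopping limits that coincide only when the course was taken through Day 15; after an earlier last dose the 28-day limit comes first and conflicts with 6.3.2

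*Protocol*

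**What the plan says.** Section 7.1 is a list in which any single item is enough: "If any of the following criteria are met, the physician in charge will discontinue protocol treatment". Item 1 sets the limit at 28 days after the last S-1 day, counting the day after that dose as Day 1, and equates it for Arm B: "which corresponds to 21 days after the scheduled start of the next course in Arm B". Item 2 applies the same count to interruptions, "If a withdrawal of more than 28 days is required", without the Arm B parenthesis. The Arm B overview in 0.3 also counts from the last dose: "If administration cannot be started more than 28 days after the last day of administration, this study treatment will be discontinued".

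The Arm B course is defined in 6.3.1: "Oral administration every day for 14 consecutive days from Day 1 (after dinner on Day 1 to after breakfast on Day 15", then a rest of 7 days, with courses repeating every 3 weeks. Section 6.3.3 (in-course withdrawal and resumption) allows a course to end early: "If the adverse event has not resolved by the end of breakfast on Day 15, no further S-1 should be administered for that course".

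Section 6.3.2 sets its own limit for starting the second and later courses. If the Table 9 criteria are not met on the scheduled day, "administration is postponed, and administration is started as soon as the patient recovers". The case is terminated "if these criteria are not met 21 days beyond the scheduled start of the next course". This limit makes no reference to the date of the last dose.

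For Arm A, 6.2.1 and 6.2.4 give only the 28-day limit.

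**The concern.** The parenthesis in 7.1(1) presents the 28-day and 21-day limits as one rule. They are counted from different points: one from the last dose, the other from the scheduled start of the next course. If dosing stops before Day 15, the first point moves earlier and, on the text shown, the second does not. A site that relies on 6.3.2, or on the stated equivalence, could restart an Arm B patient who has already met a discontinuation criterion.

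The rule decides whether treatment continues in patients aged 75 or older after a toxicity stop with slow recovery. Section 7.3 ties completion of protocol treatment to not having met 7.1, so the date on which 7.1 is met also bears on the endpoint. Any additional time for restarting would exist in Arm B only.

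**Working it through.** **Inputs**
- Last dose of a full Arm B course: Day 15, after breakfast (6.3.1).
- Scheduled start of the next course: Day 22, from the 3-week cycle (6.3.1).
- 28-day limit: the day after the last dose counts as Day 1, so the limit is Day L+28 for a last dose on Day L. That day itself is still acceptable (7.1(1), 7.1(2), 0.3).
- 21-day limit: Day 22+21 = Day 43 (6.3.2).
- Early stop: L can be less than 15 (6.3.3).

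**The plan's own figure.** With L = 15, the 28-day limit is Day 15+28 = Day 43, and 43-22 = 21 days after the scheduled start. The stated equivalence is reproduced for a full course.

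**General case.** With the next start held at Day 22:
- days from scheduled start to the 28-day limit = (L+28)-22 = L+6
- gap to the 6.3.2 limit = 43-(L+28) = 15-L days

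| Last dose (Day L) | 28-day limit | Days after scheduled start | 6.3.2 limit | Gap (days) |
|---|---|---|---|---|
| 1 | Day 29 | 7 | Day 43 | 14 |
| 8 | Day 36 | 14 | Day 43 | 7 |
| 10 | Day 38 | 16 | Day 43 | 5 |
| 14 | Day 42 | 20 | Day 43 | 1 |
| 15 | Day 43 | 21 | Day 43 | 0 |

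L+6 equals 21 only at L = 15.

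**What a site would do.** Take a last dose on Day 8, an event still unresolved at breakfast on Day 15, and Table 9 first met on Day 40. Under 6.3.2 the course starts, because Day 40 is 40-22 = 18 days past the scheduled start. Under 7.1 the patient should have been discontinued, because Day 40 is 40-8 = 32 days after the last dose. At the edge of 6.3.2, Day 43, the interval since the last dose is 43-8 = 35 days.

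**When the rules conflict.** Three things must hold together: the course ends before Day 15, Table 9 is not met through Day L+28, and it is then met by Day 43. For L = 8 the window is Days 37 to 43.

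**The case against.** The figure is correct for the prescribed course, so one can say that the parenthesis only lacks a qualifier. That is largely right, and a qualifier is most of the remedy.

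It can also be said that the early-stop case is already governed. Any one item of 7.1 suffices, 7.1(2) counts 28 days from the last dose without the parenthesis, and 0.3 repeats this for Arm B. Two stopping rules can coexist, with the earlier one binding. This stands as far as it goes: 28 days is the binding limit. It does not remove the conflict, because 6.3.2 does more than add a stopping trigger. It tells the site to start once the patient recovers, and 7.1(1) tells the site that the two limits are the same.

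The next start might be reset after an early stop. If it were set 7 days after the last dose, the two limits would agree to within a day. No text shown does this. The 3-week cycle and the Day 15 cut-off in 6.3.3 both point to a fixed Day 22, and 6.3.2 renumbers Day 1 only when a course start is postponed. The figures in 6.3 are not available, however, so a reader should not infer that the parenthesis is wrong on every possible reading.

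A reader might also infer that Arm B's completion rate is inflated. The protocol does not support that. Section 7.3 already excludes from completion anyone who met 7.1. It speaks of one year and refers to 12.2 for the detailed definition, which uses six months, but the principle is stated. Nothing in the protocol gives the number of patients who would fall in the window.

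**Conclusion.** The point holds as an inconsistency in an Arm B discontinuation rule. The equivalence in 7.1(1) is true for a course taken through Day 15 and otherwise overstates the time allowed by 15-L days: 7 days for a last dose on Day 8, 1 day for Day 14, none for Day 15. Within that gap 6.3.2 and 7.1 give opposite instructions. Arm A has no second limit.

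This rests on the next course staying scheduled for Day 22 after an early stop, which is the natural reading of the text but cannot be checked against the missing figures. The situation is narrow. The effect on the six-month completion rate cannot be quantified from the protocol and is probably small. The case for a change is that sites should have one clear stopping rule. It does not rest on any demonstrated bias in the primary comparison.

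**What to change.** In 7.1(1), qualify the Arm B parenthesis with *when the course was taken through Day 15*. In 6.3.2, put termination at 28 days from the last S-1 dose, note that this equals 21 days after the scheduled start only after a full course, and add a cross-reference to 7.1. Section 12.2 needs no addition, because 7.3 already links completion to not meeting 7.1.

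The cost is a few words in two sections, through the change procedure in 16.7. No new data are needed: the anticancer drug administration record is already collected (15.1).

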### **7.2. Follow-up for subjects who discontinued the study**

If any of the treatment discontinuation criteria are met, protocol treatment should be discontinued, and the timing, reason, and progress should be recorded in the “case report form” and evaluated up to the point of discontinuation. In addition, follow-up of adverse events should be conducted in discontinued cases until 4 weeks (day 28) after the last administration of S-1, or until the adverse events that may have been caused by the drug disappear, resolve, stabilize, or the laboratory values return to normal or stabilize.

### **7.3. Definition of Protocol treatment termination**

Protocol treatment completion is defined as completion of treatment for one year in the case of Group A or one year in the case of Group B from the start date of protocol treatment, without meeting the criteria for discontinuation of protocol treatment in Section 7.1 during the study period. See Section 12.2 for a detailed definition of completed treatment.

### **7.4. Subsequent therapy**

If any of the criteria for discontinuation of treatment in “7.1 Criteria for discontinuation of protocol treatment” are met and this treatment is discontinued, the patient should be followed up with supportive care alone until recurrence is clearly recognized, unless there is a special reason. Although treatment in the event of recurrence or the presence of cancerous lesions other than recurrence will not be restricted, the details should be reported in the case report form.

## **8. Concomitant medications, and concomitant and supportive care**

### **8.1. Prohibited concomitant drugs and prohibited therapies**

Other anticancer drugs, flucytosine, phenytoin, warfarin, dabigatran, radiation therapy, immunotherapy, surgery, hormones

